In a non-pre-specified analysis of the Targeted Oxygen in the Resuscitation of Preterm Infants Trial, infants of < 28 weeks’ gestation who received an initial FiO_2_ of 0.21 at resuscitation had higher hospital mortality than those given an initial FiO_2_ of 1.0 (10/46 [22%] vs. 3/54 [6%]; RR: 3.9 [95% CI: 1.1–13.4]; *p* = 0.01) [23]. Furthermore, the most recent individual patient analysis of eight trials reported that infants who were started with an initial FiO_2_ of < 0.3 had significantly lower 5 min SpO_2_ values compared to infants started with an initial FiO_2_ of ≥ 0.6 [35]. Furthermore, infants initially resuscitated with initial FiO_2_ of 0.21–0.3 compared to initial FiO_2_ of ≥ 0.6 had an increased risk of major intraventricular hemorrhage and a five times higher risk of death [35]. Similarly, if preterm infants resuscitated with initial low FiO_2_ do not reach SpO_2_ of 80% at 5 min, it was associated with increased risk of major intraventricular hemorrhage and an almost five times higher risk of death [35]. There is equally growing evidence that using lower initial FiO_2_ will lead to lower SpO_2_ levels and bradycardia, which may lead to increased rates of mortality in this vulnerable group of infants [34, 36]. These data provide a warning note for the use of higher vs. lower initial FiO_2_ during delivery room resuscitation. Trials are urgently needed to evaluate the risk of using low and high initial FiO_2_ in preterm infant stabilization at birth [37]. In summary, the “optimal” FiO_2_ used to initiate post birth stabilization of extreme preterm seems to be about balancing the need to quickly achieve target saturations while minimizing the oxidative stress of “too much” oxygen.

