#### ***Initial FiO***_***2***_*** of 0.6 arm***

Infants randomized to this arm will receive initial FiO_2_ of 0.6 during the first 3 min of life. Focus will be on providing effective ventilation. During this time, if SpO_2_ is available and reliable, oxygen may be increased by 20% every minute if an SpO_2_ ≥ 85% is unlikely to be achieved by 5 min. Once a reliable SpO_2_ reading is available, or at the latest at 3 min of age, the clinical team will assess SpO_2_. If SpO_2_ is < 85%, oxygen should be increased by 20% every 60 s to achieve SpO_2_ ≥ 85% at 5 min of age. If SpO_2_ is > 95% at or before 5 min of age, oxygen should be decreased by 10–20% every 60 s to maintain SpO_2_ of ≥ 85%. At 10 min of age and beyond, aim for SpO_2_ of 90–95% or as per institutional guidelines. If, at any time during the resuscitation, the HR is 60–100 and not increasing with effective ventilation, oxygen will be increased by 20% every min, regardless of SpO_2_ (Fig. 1).

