### Duration of treatment period

The study intervention duration will be the first 10 min after birth.

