### Sample size {14}

A sample size of 1200 (600 per group, adjusted for 10% loss of follow-up) infants has been determined based on: baseline outcome rate of 35% (18% mortality and 17% abnormal neurodevelopmental outcomes) [48], RRR of 25%, type I error of 5%, power of 80%, within-cluster within-period ICC of 0.034, within-cluster between-period ICC of 0.029, cluster size in each arm of 10–80 (unequal cluster period but equal cluster size), and loss to follow-up rate of ~ 10%. ICCs were derived from existing data from the Canadian Neonatal Network sites [48]. With these assumptions, we will need up to 20 centers (clusters) to recruit 20–80 patients per arm (20–160/center) for a total of 1200 neonates at all sites.

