### Implementation {16c}

Before the start of the trial, the statistician will use computer-generated random numbers to prepare the allocation sequence for all participating centers by producing the codes and allocation table, which then will be validated by an independent statistician. Clinical staff attending neonatal deliveries know the group assignment and will enroll every participant automatically, as the group assignment is also local hospital policy.

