## Statistical methods

### Statistical methods for primary and secondary outcomes {20a}

A detailed statistical analysis plan will be finalized and submitted for publication prior to database lock. Data handling, verification, and analysis for the HiLo trial will be performed by WCHRI. Statistical analysis will follow standard methods for randomized trials, and reporting of findings will be performed in accordance with CONSORT guidelines extension for cluster trials [51].

The primary analysis will be conducted using an “intention-to-treat” approach. For the primary outcome, generalized linear mixed model with binary outcome and maximum likelihood estimate will be used to evaluate the effect of an oxygen concentration on the primary outcome. To account for cluster crossover design of the study, effects of centers (clusters) and a period (oxygen concentration) within center will be considered random, and effects of the intervention (oxygen concentration) will be entered as a fixed effect. This hierarchical model allows for the correlation of patients within periods and within clusters. The model will be adjusted for gestational age and if the infant required mask ventilation as potential confounding variables. To account for multiple births when more than one infant is enrolled in the study, clustering within mothers will be entered as a random effect in the model and this model will be tested for a better fit.

Similar generalized linear mixed models will be performed to evaluate the effect of group on secondary outcomes. If convergence problems arise, different fitting techniques will be used depending on the nature of the problem. For example, different approximation methods (e.g., maximum likelihood or pseudo-likelihood methods) will be tried; different types of covariance structures will be used. In addition, in case of singularity of variance–covariance matrix, models with fewer random effects will be created if the fit is adequate.

Analysis of secondary outcomes will use generalized linear mixed models or descriptive analysis. Summary statistics will be presented for baseline and clinical characteristics: continuous data by mean, two-sided 95% CI of the mean, standard deviation, median, interquartile range (first and third quartiles), minimum and maximum. Categorical data will be presented by absolute and relative frequencies.

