### Methods for additional analyses (e.g., subgroup analyses) {20b}

For the primary outcome, the following subgroups will be analyzed: (i) gestational age 23^+0^–25^+6^ vs. 26^+0^–28^+6^; (ii) infants supported with CPAP vs. received mask ventilation [52]; (iii) female vs. male [53, 54].

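### The primary model adjusts for mask ventilation, a status that arises after a known allocation, so the estimate can depart from the total effect of initial FiO2 if the arm changes ventilation

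*Protocol article*

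**What the plan says.** Under Statistical methods for primary and secondary outcomes {20a}, the protocol article says: "The primary analysis will be conducted using an “intention-to-treat” approach". In the same paragraph it fixes the covariates: "The model will be adjusted for gestational age and if the infant required mask ventilation as potential confounding variables". It gives no time point for the mask-ventilation variable, does not restrict it to a status before allocation, and states no primary model without it. Similar models are planned for the secondary outcomes, with no covariates named.

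Other sections place mask ventilation in time:

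- Initial FiO2 of 0.6 arm: "Infants randomized to this arm will receive initial FiO_2_ of 0.6 during the first 3 min of life". The 0.3 arm has parallel wording.
- Duration of treatment period: "The study intervention duration will be the first 10 min after birth".
- Implementation {16c}: "Clinical staff attending neonatal deliveries know the group assignment".
- Secondary outcomes: the proportion of infants on mask ventilation, as against breathing spontaneously, is an outcome at 3 and at 5 minutes.
- Methods for additional analyses {20b}: a subgroup comparison of "infants supported with CPAP vs. received mask ventilation".

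The Primary research question asks whether starting resuscitation at 0.6 rather than 0.3 changes the incidence of death or major neurodevelopmental outcome. That is a question about the whole effect of the starting concentration.

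**The concern.** Covariates in the primary model of a randomised trial should be fixed before allocation, or at least be beyond its influence. Mask ventilation meets neither condition here. It is decided in the same minutes in which the allocated oxygen is given, by staff who know which oxygen that is.

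If the arm alters how many infants are mask ventilated, conditioning on ventilation does two things. It removes whatever part of the effect runs through ventilation. It also compares infants who reached the same ventilation status under different arms, and these may differ in unmeasured severity even though the arms were balanced. The first usually pulls a real effect towards the null. The second can produce an apparent effect where none exists. At stake is the trial's main estimate, and any secondary estimate from a model with the same covariate.

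**Working it through.** **1. The plan's own figure.** Sample size {14} gives "A sample size of 1200 (600 per group, adjusted for 10% loss of follow-up) infants". Its inputs are 35% in the control arm, a 25% relative reduction (the Abstract states 26.5%), 5% type I error (two-sided assumed), 80% power, ICCs of 0.034 within period and 0.029 between periods, and 10% loss. For 35% versus 26.5%, the two-proportion formula gives 462 per arm. The cluster-crossover design effect is 1 + (m − 1) × 0.034 − m × 0.029, where m is the cluster-period size. Only a range is given for m, so its value is an assumption.

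- m = 40: design effect 1.166; 462 × 1.166 ≈ 539 per arm, 1078 in total; 1078 / 0.9 ≈ 1198.
- m = 30: design effect 1.116; 516 per arm, 1032 in total; 1032 / 0.9 ≈ 1147. With an assumed cluster-size coefficient of variation of 0.6, the total becomes 1202.

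So 1200 is reproduced under ordinary choices. None of the listed inputs is a covariate, so removing one from the model does not change it.

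**2. How much the coefficient could move.** The protocol has no ventilation rates by arm, so the following are assumptions: 75% ventilated in the 0.3 arm, a conditional odds ratio of 2.5 between ventilation and the outcome, and overall risks of 35% and 26.25% (35% × 0.75). For each arm, solve for the intercept a in

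risk = p × expit(a + ln 2.5) + (1 − p) × expit(a),

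where p is the proportion ventilated. The adjusted log odds ratio is the difference between the two intercepts. The 0.3 arm has a = −1.334. Without ventilation in the model, the odds ratio is (0.2625/0.7375)/(0.35/0.65) = 0.661, log −0.414. Power is approximated as Φ(2.80 × ratio − 1.96), where 2.80 = 1.96 + 0.84 and the standard error is held fixed.

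| Ventilated, 0.6 arm | Intercept | Adjusted OR | Share of log OR kept | Power |
|---|---|---|---|---|
| 75% | −1.759 | 0.654 | 103% | no loss |
| 70% | −1.717 | 0.681 | 93% | 74% |
| 65% | −1.675 | 0.711 | 82% | 64% |
| 60% | −1.632 | 0.742 | 72% | 52% |

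The 103% in the first row is non-collapsibility of the odds ratio, not bias. Using 26.5% in place of 26.25% changes the last three shares only to 92%, 82% and 71%.

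**3. Unmeasured severity.** Now assume a severity factor present in half the infants, with an odds ratio of 3 for both ventilation and outcome, 70% ventilated in the 0.3 arm, and 35% control risk.

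- No effect of arm or ventilation on the outcome (true OR 1.00): the adjusted OR is 1.00 if the 0.6 arm also has 70% ventilated, 1.014 at 65%, 1.029 at 60% and 1.059 at 50%.
- Ventilation on the causal path (OR 2), no direct effect of arm: a total OR of 0.942 becomes 1.029 at 60%, and 0.885 becomes 1.059 at 50%. A protective total effect then appears as slight harm.
- Direct OR 0.66 plus the same path: 0.646 becomes 0.695 at 60%, and 0.607 becomes 0.715 at 50%. Part of this gap is non-collapsibility.

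In every scenario the distortion depends on a difference in ventilation between arms.

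**The case against.** A reader might infer that the primary estimate is certain to be biased. The protocol does not support that. Distortion requires the arm to change the use of mask ventilation, and no rates by arm are given. With equal ventilation, the null estimate stays at 1.00 even with strong unmeasured severity, and the adjusted effect loses nothing. The fall to 52% power belongs to one assumed scenario, a 15-point difference, and is not a forecast.

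A reader might also take the background as saying that low starting oxygen leads to mask ventilation. Summary of current evidence says that "using lower initial FiO_2_ will lead to lower SpO_2_ levels and bradycardia, which may lead to increased rates of mortality"; it does not mention ventilation at that point. In the arm descriptions, the stated response to low saturation, or to a heart rate that fails to rise with effective ventilation, is more oxygen. Ventilation may also begin together with the allocated oxygen. A path from arm to ventilation is plausible, not documented, though even an early decision to ventilate follows a known allocation.

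Nor are the covariate and the secondary outcome shown to be the same variable. One is need for mask ventilation with no time point; the other is status at 3 and 5 minutes. They overlap.

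The wish to adjust for severity is understandable. Up to 20 centres are randomised, the arm is known, and consent is sought after the intervention, so case mix could differ by arm. That supports adjusting for characteristics fixed before allocation. It does not support a variable that the arm may itself influence.

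Finally, a detailed analysis plan is due before database lock and may define the variable or drop it. The published protocol would still state the present rule and need correcting.

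**Conclusion.** The point holds as a risk written into the primary analysis. The model conditions on a status that arises after a known allocation, inside the intervention window, and that overlaps one of the trial's own outcomes. If the arm changes ventilation, the coefficient does not answer the primary research question, and its size and direction of error cannot be known in advance. Under the assumptions above, the share of the log odds ratio kept runs from all of it (equal ventilation) to about 72% (a 15-point difference), with power between no loss and about 52%. These figures show scale only, since the ventilation rates, the odds ratio of 2.5 and the severity factor are all assumed. Whether ventilation differs by arm is something the trial sets out to learn, so its primary estimate should not rely on the answer being no.

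**What to change.** Remove mask ventilation from the primary model, and from any secondary-outcome model that would otherwise carry the same covariate. Keep gestational age and, if more adjustment is wanted, add variables fixed before allocation, such as sex. Report mask ventilation by arm as an outcome. If a model including it is of interest, define the time point and label the model supplementary or exploratory. The subgroup of CPAP versus mask ventilation rests on the same post-allocation status and should carry the same caution.

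The cost is a sentence in the protocol and its counterpart in the analysis plan. No extra infants or data are needed. The protocol leaves the analysis plan open until before database lock and expects results in late 2028, so the change can still be prespecified.

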**Enrolment**					
Eligibility screen	X	X			
Informed consent			X	X	
Maternal demographic and pregnancy data			X		
Randomization data		X			
Baseline infant data			X	X	

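### The primary model has gestational age as its only covariate fixed before oxygen starts; pre-specifying infant sex too would bring a small, low-cost gain

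*Protocol article*

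**What the plan says.** Under Statistical methods {20a} the primary outcome is analysed by a generalized linear mixed model with the intervention as a fixed effect. On the random part the article states that "effects of centers (clusters) and a period (oxygen concentration) within center will be considered random"; a random effect for mother is to be tried as well. On covariates it states: "The model will be adjusted for gestational age and if the infant required mask ventilation as potential confounding variables". A detailed statistical analysis plan is promised before database lock.

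Three other places bear on the point:

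- Additional analyses {20b} lists three subgroups for the primary outcome: gestational age, CPAP versus mask ventilation, and "iii) female vs. male". The first two factors are also model covariates; the third is not.
- The participant timeline {13} shows that "Maternal demographic and pregnancy data" and "Baseline infant data" are collected. It does not name the variables.
- The intervention covers the first 10 minutes after birth {11a}, and mask ventilation status at 3 and 5 minutes is a secondary outcome {12}.

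**The concern.** Mask ventilation is observed during the intervention, so the listed set contains one covariate that the oxygen cannot have affected. Whether mask ventilation belongs in the model at all is a separate and more serious question; this point concerns what is missing beside gestational age.

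Sex is known at birth, is on file, and is thought relevant enough to the primary outcome to define a subgroup. Leaving a prognostic baseline variable out of a pre-specified model gives up a little power. It also leaves any measured imbalance in that variable uncorrected.

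The design gives the second reason some weight. Treatment is assigned by period in at most 20 centres, not infant by infant. Periods can differ in length, because a centre switches once its first-arm target is met. Staff know the allocation. Consent is sought after the intervention, and infants whose parents refuse or cannot be approached are excluded. The case mix of a centre's two periods can therefore differ. The random period-within-centre effect carries such variation into the standard error but does not correct the estimate for it.

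**Working it through.** **1. The plan's own figure.** Sample size {14} gives "baseline outcome rate of 35% (18% mortality and 17% abnormal neurodevelopmental outcomes" and "RRR of 25%, type I error of 5%, power of 80" per cent, ICCs of 0.034 (within period) and 0.029 (between periods), and 10% loss. The abstract gives 35% versus 26.5%; a 25% reduction from 35% is 26.25%.

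- Two proportions, 35% v 26.5%, two-sided 5% (assumed), 80% power, pooled variance: 462 per arm, 924 in all.
- Design effect with *m* infants per centre-period: 1 + (*m* − 1) × 0.034 − *m* × 0.029.
- *m* = 40: 1.166, so 924 × 1.166 = 1077, and 1077 / 0.90 = 1197.
- *m* = 30 (1200 over 20 centres and 2 periods): 1.116, giving 1146.

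The stated 1200 is reproduced at *m* = 40, an assumption that stands for unequal sizes around a mean of 30. No covariate gain is used.

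**2. Gain from sex, by hand.** For a logistic model the proportional efficiency gain is about *p*(1 − *p*) × the variance that the new covariate adds to the linear predictor. With *p* = (0.35 + 0.265)/2 = 0.3075, *p*(1 − *p*) = 0.213. For a 50:50 factor with log odds ratio *b* the variance is *b*²/4. The article gives no effect for sex, so a range is assumed.

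| Odds ratio for sex | *b* | *b*²/4 | Gain |
|---|---|---|---|
| 1.2 | 0.182 | 0.0083 | 0.2% |
| 1.5 | 0.405 | 0.0411 | 0.9% |
| 1.8 | 0.588 | 0.0864 | 1.8% |

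**3. Gain by large-sample logistic models.** Inputs: 540 evaluable per arm, design effect 1.116, risk under 0.6 of 26.5% or 26.25%, gestational age odds ratio 1.3 to 1.8 per week earlier, sex 1.2 to 1.8, and a score for all other baseline predictors. Sex beyond gestational age gains 0.1 to 1.7%, at most 0.6 power points (for example 0.828 to 0.834). Gestational age, already in the model, brings about 1 to 6 points over no adjustment.

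| Odds ratio per SD of the other-predictor score | Gain of sex plus score over gestational age | Power points |
|---|---|---|
| 1.2 | 0.8–2.4% | 0.2–0.9 |
| 1.5 | 3.2–4.9% | 0.9–1.7 |
| 2.0 | 8.7–10.7% | 2.4–3.6 |

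**4. Named further predictors.** Simulation (1500 trials per scenario, 860 effective infants, logistic models) assumed log odds of 0.4–0.5 for sex, 0.3–0.4 per SD for birth weight for gestation and 0.5–0.7 for antenatal steroids. It gave 1.1% for sex, 2.8% with birth weight, and 3.8 to 5.6% with steroids as well. The hand formula agrees at the lower values for sex and birth weight: 0.213 × (0.4²/4 + 0.3²) = 0.213 × 0.13 = 2.8%. In infants, 1.1% of 1200 is 13 and 5.6% is 67.

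**5. Chance imbalance in sex.** With 600 per arm the SD of the difference in the proportion of boys is √(2 × 0.25/600) = 2.9 percentage points, so 2 SD is 5.8 points. The shift in risk difference is about 0.058 × *b* × 0.213: 0.2 points at odds ratio 1.2 and 0.7 points at 1.8, against a target of 8.5. This treats infants as independent; drift within centres could make the imbalance larger.

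**The case against.** The strongest reply is that a short covariate list is a choice, not an error. Using sex as a subgroup factor does not oblige the plan to adjust for it, and the analysis plan, not seen here, may extend the list. It is true that nothing is contradicted. But the article does not leave the list open: it states it, and leaves out a baseline variable that the trial holds. That supports a suggestion, not a charge of error.

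The reply on size also stands. For sex, the only further predictor that the article names, the gain is under one power point. The larger figures rest on variables that the article never names as collected and on effects that it does not give. The calculations also used logistic models with at most a design-effect correction, not the planned mixed model.

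A reader might infer more than the documents support:

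- **That the trial is underpowered as planned.** It is not on this account: step 1 reproduces 1200 without any covariate gain.
- **That baseline data go unused.** Baseline characteristics are to be summarised, and sex is used for a subgroup.
- **That adjustment is free.** Added covariates change the conditional odds ratio being estimated, and {20a} already foresees convergence problems and singular covariance matrices.
- **That adjustment removes drift between periods.** It corrects only measured imbalance. The 1:1 allocation to the two orders already balances a common time trend in expectation, and each centre is its own control.

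**Conclusion.** The point holds as a minor improvement. Gestational age is the only covariate in the primary model that is fixed before the oxygen starts, and sex could join it at little cost. The expected gain is about 0 to 2% in efficiency (at most 0.6 power points) from sex, and roughly 3 to 6% (up to about 2 power points) with further predictors of the assumed strength. A gain of about 3 points would need other predictors with a combined odds ratio near 2 per SD beyond gestational age, and the documents give no basis for assuming that. The second benefit is partial protection against measured case-mix differences between a centre's two periods; for chance imbalance in sex alone, that is worth a few tenths of a percentage point in the risk difference. All the gains rest on assumed prognostic effects.

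**What to change.** In the analysis plan, before database lock, list gestational age (continuous) and infant sex as fixed effects in the primary model and in the models for binary secondary outcomes. Add other strong predictors fixed before the oxygen starts, such as birth weight for gestational age and antenatal steroid exposure, only if the case report form records them. Fix the set in advance, so that covariates are not chosen after imbalances are seen.

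Because the conditional odds ratio depends on the covariate set, a marginal risk difference or risk ratio from the same model could be reported alongside; it also matches the scale on which the trial was sized.

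The cost is a line or two of text. Adding sex needs no new data. The small downside is a slightly more complex mixed model.
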